## Discussion

BAD-study will be the first prospective clinical-radiological cohort with long-term follow-up and large sample, focusing on the BAD-related stroke, a neglected but clinically meaning subtype of stroke in Asians with poor collateral circulation and high disability [4, 10, 40]. The demographic clinical, radiological, and prognostic characteristics of BAD-related stroke in China will be reported.

In addition, we noticed that the BAD-related stroke was categorized as “stroke of undetermined etiology” in TOAST classification system, and thus failed to reflect its underlying stroke mechanism [4, 6, 40]. Our study will update the original TOAST classification, and prove the concept of BAD-related stroke. In addition, we noticed the higher frequency of cardiogenic embolism in elderly patients with lacunar infarcts, and excluded patients with cardiogenic stroke in our study [41].

With the documented data of laboratory tests, the role of inflammatory indicators on the prognosis of stroke will be assessed. The management of inflammatory indicators might be a novel therapy on reducing END and improving the outcome of BAD-related stroke [12, 28, 29, 31].

With the aid of MRI, MRA, HR-MRI, and ASL, BAD-study will analyze the cerebral artery, vessel wall of parent artery and penetrating artery, artery plaques, brain tissue, cerebral perfusion, and volume of lesion in BAD-related stroke. In addition, visualized analysis of LSA, and its association with outcomes will help neurologists understand the vascular mechanism of END [35, 42]. Radiological data of artery and lesion will provide clues for possible effective drugs. Moreover, quantitative analysis will be conducted to analyze the effect of lesion on the volume of gray matter and white matter, as global brain inflammation could be elicited by localized lesion [43, 44]

Besides, the comparison of different therapy strategies on primary outcome and END will provide direct clinical evidence to optimize the acute therapy in BAD-related stroke [13] and find the probably effective strategy of preventing END [12]. Based on the results of BAD-study, a risk prediction model will be generated for the prognosis, which may help neurologists individualize treatment strategy.

BAD-study will also assess the efficacy and safety of tirofiban, providing baseline data for further randomized controlled trials in patients with BAD-related stroke. And the diagnostic criteria of BAD-related stroke will be verified in clinical practice [7–9].

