## Methods/design

### Study design

BAD-study is a nationwide, multicenter, consecutive, prospective, observational, cohort study recruiting patients with BAD-related stroke within 72 h after symptom onset. Due to February 28, 2022, this ongoing study has recruited 22 hospitals with the equipment of 3 Tesla (T) magnetic resonance imaging, with the leader of Peking Union Medical College Hospital in Beijing, China. BAD-study was approved by the Ethics Committee of Peking Union Medical College Hospital on May 25, 2021 (No. ZS-2982B), and written informed consents (model consent form) are required for all patients. In addition, protocol modifications, if any, would be approved by the ethics committee. The anticipated duration of the study will be about 2 years from June 1, 2021 until May 31, 2023. BAD-study has been registered on July 28, 2021 at clinicaltrials.gov, with identifier NCT04973774.

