### Study objectives

The primary objective of this study is to figure out the demographic, clinical, radiological characteristics, risk factors, and prognosis of BAD-related stroke in this clinical-radiological cohort with large sample, and evaluate the effects of different real-word therapies on outcome. Secondary objectives are to: 1) investigate the vascular mechanism of END; 2) establish the association between clinical, clinical, radiological characteristics and clinical outcome and model for predicting outcome; 3) find out the standardized process and criteria for analyzing penetrating arteries using vessel wall imaging (VWI) based on 3 Tesla-MRI; 4) explore the efficacy of safety of specific drugs, such as aspirin and tirofiban, providing baseline data for further clinical trials.

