### Study measurements

#### Clinical data

Data of patients will be collected and reported using the electronic Case Report Form (e-CRF) at baseline and follow-up periods. The quality of data will be monitored dynamically by the central center. Clinical items include demographics, medical history, history of medication, clinical presentations, and treatments in hospital. The blood pressure and intake and output volume within 72 h after enrollment are also recorded. The details is shown in Table 1.

**Table 1 Tab1:** Clinical assessment of BAD-related stroke

Items	Assessment
Demographics	Age, gender
Medications prior to stroke	Antiplatelet drugs, statins, anticoagulant drugs, and tirofiban
Medical history	Stroke, hypertension, diabetes mellitus, dyslipidemia, heart disease, chronic respiratory disease, autoimmune diseases, blood system disorders, and thyroid disorder
Personal history	Smoking, alcohol use, and daily activity
Family history	Cardiovascular and cerebrovascular diseases
Current stroke onset	
Time information	Time of symptom onset, arrival at hospital, and enrollment
Stroke symptom	Types (ischemic stroke or transient ischemic attack [TIA]), and presentation (pure motor hemiparesis, pure sensory, sensorimotor syndrome, and others)
Blood pressure	(1) Arrival at hospital, enrollment, and each follow up; (2) Monitor of blood pressure within 72 h after enrollment (≥ 3 times per day, interval time ≥ 2 h)
Heart rate	Arrival at hospital, enrollment, and each follow up
Intake and output volume	Monitor of intake and output volume within 72 h after enrollment
Stroke severity	National Institutes of Health Stroke Scale
Functional assessment	mRS
Activities of daily living	Barthel index
Reperfusion therapy	Data of intravenous thrombolysis, and change of NIHSS score
Medications after stroke	Antiplatelet drugs, lipid-lowering drugs including statins, anticoagulant drugs, antihypertensive drugs, antidiabetics, and other neuroprotective drugs
END	Therapies for END, and time of END occurrence
Use of tirofiban	Time, dosage, duration and side effects

*END* Early neurological deterioration, *TIA* Transient ischemic attack, *mRS* Modified Ranking scale, *NIHSS* National institute of health stroke scale

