### Outcome measures

The primary outcome in our study is the score on the modified Rankin scale at 90 days, which is a 7-point scale ranging from 0 (no symptoms) to 6 (death) [36]. Secondary outcomes include END within 7 days, and NIHSS score, Barthel index, cerebrovascular events (myocardial infarction, new-onset ischemic stroke, new-onset intracranial hemorrhage), and major bleeding complications measured by PLATO (Platelet Inhibition and Patient Outcomes) definition during 90-day follow-up [37]. All-cause mortality within 90 days is also recorded. The follow up times are extended to 1 year, as the long-term outcome of BAD-related stroke remains inconclusive [4, 6].

The END is defined as: 1) From symptom onset to 7 days after enrollment; and 2) Occurrence of deterioration of neurologic deficits after initial assessment: A. An increase of the NIHSS score ≥ 4 points or the NIHSS motor score ≥ 1 point for ischemic patients; or B. The stereotyped attacks still repeat ≥ 3 times after arrival at hospital or progress to persistence status for patients with internal capsule warning syndrome or pontine warning syndrome [12, 38].

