### Statistical analysis

Categorical variables will be presented as frequencies and percentages, such as gender, vascular risk factors, lesions of penetrating artery, and therapies. Continuous variables with non-normal distributions will be shown as median and interquartile range (IQR), while continuous variables with normal distributions as mean and 95% confidence interval (CI), such as age, NIHSS score, blood pressure, and hemoglobin concentration. For the statistical significance analysis of the outcomes, Pearson χ 2 or Fisher’s exact test, Wilcoxon tests, and t-tests will be used, where appropriate, with statistical uncertainty expressed by means of 95% CI. Cox proportional hazards model, Logistic regression model, and Poisson regression model will be used to assess the association between outcomes and clinical or radiological predictors, where appropriate. The good prognosis is defined as 0–2 mRS score, and poor prognosis as 3–6 mRS score at 90 days. Predictors including clinical and radiological features and different treatments will be evaluated. All analysis will be performed using SAS 9.4 and two-sided *P* < 0.05 is considered significant.

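### Treatment effects on END and 90-day mRS are claimed as direct evidence, with no rule that treatment must precede the END it is credited with preventing

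*Protocol article*

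**What the plan says.** - **Design.** "BAD-study is a nationwide, multicenter, consecutive, prospective, observational, cohort study recruiting patients with BAD-related stroke within 72 h after symptom onset" (Study design). Treatment is whatever the hospitals give.
- **Objectives.** Part of the primary objective is to "evaluate the effects of different real-word therapies on outcome". A secondary objective is to "explore the efficacy of safety of specific drugs, such as aspirin and tirofiban" (Study objectives).
- **Outcome.** END is counted "From symptom onset to 7 days after enrollment", and the worsening must also come after the initial assessment (Outcome measures). It is ascertained at the day-7 visit by looking back to stroke onset (Procedures).
- **Data.** Table 1 has one row for "Therapies for END, and time of END occurrence", another for tirofiban use that includes its timing, and another for medications after stroke. That last row names no start time.
- **Analysis.** After listing simple tests and Cox, logistic and Poisson models, the section says "Predictors including clinical and radiological features and different treatments will be evaluated" (Statistical analysis).
- **Reading of the result.** "the comparison of different therapy strategies on primary outcome and END will provide direct clinical evidence to optimize the acute therapy", and "BAD-study will also assess the efficacy and safety of tirofiban" (both Discussion). The first sentence goes on to say that the comparison should help find a strategy against END.

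**The concern.** A treatment given because a patient has deteriorated cannot have prevented that deterioration. If it counts as exposure for the same END, the drug looks harmful through the order of events alone. The effect carries over to 90-day mRS, because the Background describes END as strongly tied to poor outcome. Adjusting for baseline severity, which the named models allow, does not remove this: the problem is timing, not imbalance. Confounding by indication comes on top.

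Therapy effect is part of the primary objective, and the results are meant to inform randomised trials. A misleading direction of effect could lead those trials to drop a useful drug or pursue a useless one.

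**Working it through.** The article gives no figure for any treatment contrast. Its one design figure, the sample size, reproduces: 450 × 1.10 = 495 (450/0.90 would give 500). That is not in dispute; n = 450 is used below only for error rates.

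**1. Order of events in the text.** The END window in effect opens at the initial assessment. Among the first 143 patients, enrolment came a median of 48 h after onset (IQR 30–65; Table 3). If the initial assessment is the one on arrival, both END and the start of a drug can precede enrolment, in either order. Table 1 shows that the investigators expect some therapy to be a response to END.

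**2. Apparent effect of a null drug on END.** These are assumptions, not figures from the article:
- a share *a* receives the drug regardless of END;
- a share *b* of the remaining END patients receives it because of END;
- exposure is coded ever versus never.

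Then P(drug | END) = a + (1 − a)b and P(drug | no END) = a, so

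OR = [a + (1 − a)b] / [a(1 − b)].

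For a = 0.20 and b = 0.10: P(drug | END) = 0.20 + 0.80 × 0.10 = 0.28, and OR = (0.28/0.72)/(0.20/0.80) = 1.56.

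| b | OR, a = 20% | OR, a = 10% |
|---|---|---|
| 0 | 1.00 | 1.00 |
| 10% | 1.56 | 2.11 |
| 30% | 3.14 | 5.29 |
| 50% | 6.00 | 11.00 |

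The END rate cancels out of these odds ratios.

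**3. False positives.** Simulation with n = 450, a = 20%, Pearson chi-square, two-sided 0.05 and 2,000 runs. The END rate was 13.8% or 30%. The first is the Background figure for END at 24 h after thrombolysis, a narrower definition than this study's; the second is assumed. Rejection rates were about 5% at b = 0, 30% to 47% at b = 10%, and 97% to nearly 100% at b = 30%.

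**4. A drug that works.** With a true OR of 0.60 for END and a = 20%, the apparent OR is 1.06–1.09 at b = 10% and 2.37–2.48 at b = 30%. Counting only treatment started regardless of END (b = 0) returns 0.60.

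**5. 90-day mRS.** Assume a poor outcome in 60% with END and 20% without, and a null drug. At END 13.8%, a = 20% and b = 10%:
- P(END | drug) = 0.138 × 0.28 / (0.138 × 0.28 + 0.862 × 0.20) = 0.183
- P(END | no drug) = 0.138 × 0.72 / (0.138 × 0.72 + 0.862 × 0.80) = 0.126
- Poor outcome: 27.3% versus 25.0%, OR 1.13

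Over both END rates the OR is 1.13–1.19 at b = 10% and 1.38–1.57 at b = 30%.

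**6. The opposite coding.** Suppose patients who start the drug after END are relabelled untreated. Assume 15% planned use, exponential times, mean time to END 36 h and mean planned start *m* hours. Among planned users with END, a share s = 36/(36 + m) starts first, so OR = [0.15s/(1 − 0.15s)]/(0.15/0.85). For m = 36, 12, 6 and 1 h this gives 0.46, 0.72, 0.84 and 0.97. The apparent protection depends almost wholly on how late planned treatment starts.

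**The case against.** The strongest reply is that the article is a condensed account. The covariate list, any propensity score and the coding of treatment belong in an analysis plan that is not shown, so their absence is no fault. That stands, and this point does not rest on it. Table 1 also keeps therapies for END apart from other medication and times both END and tirofiban, so the study collects part of what a sound analysis needs. The wording is hedged in places: one objective is to explore, the models are said to assess association, and the Sample size section disclaims a specific hypothesis.

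A reader might infer more than the documents support:
- **That tirofiban is a rescue drug here.** No section says which drugs are given for END. Tirofiban is only a plausible example.
- **That rescue and initial treatment will be pooled as ever versus never.** The article does not state the coding. The odds ratios show what follows if that coding is used.
- **That any worsening since onset counts as END.** The definition also requires it to follow the initial assessment.
- **That the opposite, protective bias is large.** It is near zero when planned treatment starts early.

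What the reply does not answer is the mismatch within the article. It states a causal aim, lists treatments among ordinary predictors, acknowledges therapy triggered by the outcome, and still calls the comparison direct evidence. An unseen plan could improve the analysis but would not make that description right.

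**Conclusion.** The point holds and should be fixed. As written, the claims about preventing END and about drug efficacy do not follow from the comparison described, because nothing stated makes treatment precede END and treatment is not randomised.

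The size is illustrative. Under ever/never coding with 20% baseline use, a null drug shows an OR for END of 1.56 if 10% of the remaining END patients are treated because of END, and 3.14 if 30% are. The bias in mRS is smaller and rests on further assumed outcome rates. All treatment shares are assumptions, so the direction under that coding is firm and the magnitude is not. The documents do not establish that the final analysis will be biased, or that any named drug will be affected.

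**What to change.** 1. **END.** Start follow-up at the initial assessment and enter treatment as a time-dependent covariate in the Cox model already named, so that a drug begun at or after END never counts as exposure for that END. Do this for drugs with a recorded start time (tirofiban, on Table 1). Make no END-prevention claim for drugs without one.
2. **90-day mRS.** Set a fixed landmark after the initial assessment. Restrict to patients free of END at that time, and classify them by the treatment they are on then, whatever happens later. Report therapies given for END separately. Defining initial treatment merely as treatment before END would relabel rescue users as untreated and bring back the bias in step 6.
3. **Confounding.** Adjust treatment contrasts for factors measured before treatment: NIHSS where available, age, onset-to-arrival time, LSA or PPA territory, thrombolysis, and centre. Table 1 does not tie NIHSS to treatment start and Table 3 gives it at enrolment, so state whose score precedes treatment.
4. **Risk model.** Leave post-END therapy out of the baseline prediction model.
5. **Wording.** In Study objectives and Discussion, replace the language of direct evidence and efficacy with exploratory adjusted associations.

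The work is mainly wording and programming; END time and tirofiban time are already collected. The price is more modest claims and a smaller set of END comparisons. Aspirin, which the objectives name, may lose its END comparison if its start time is not recorded. The landmark analysis also excludes patients with earlier END.

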## Data Availability

The data of BAD-study will be available from the corresponding author on reasonable request.

## Abbreviations

ADC: Apparent diffusion coefficient
ASL: Arterial spin labeling
BAD: Branch atheromatous disease
CCA: Common carotid artery
CI: Confidence interval
CTA: Computed tomography angiography
DSA: Digital subtraction angiography
DWI: Diffusion weighted imaging
e-CRF: Electronic case report form
ECG: Electrocardiograph
END: Early neurological deterioration
FA: Flip angle
FLAIR: Fluid attenuated inversion recovery
FOV: Field of view
HR-MRI: High-resolution magnetic resonance imaging
ICA: Internal carotid artery
IQR: Interquartile range
LACI: Lacunar infarction
LAD: Large artery disease
LD: Labeling duration
LSA: Lenticulostriate artery
MRA: Magnetic resonance angiography
MRI: Magnetic resonance imaging
mRS: Modified Ranking scale
NIHSS: National institute of health stroke scale
pCASL: Pseudo-continuous arterial spin labelling
PLATO: Platelet Inhibition and Patient Outcomes
PLD: Post-labeling delay
PPA: Paramedian pontine artery
SWI: Susceptibility weighted imaging
SubA: Subclavian artery
T: Tesla
TCD: Transcranial Doppler
TE: Echo time
TI: Inversion time
TIA: Transient ischemic attack
TOF-MRA: Time-of-flight MR angiography
VA: Vertebral artery
TR: Repetition time
VWI: Vessel wall imaging
